### Secondary outcome measures

A number of secondary measures are used (Table 3), including an 11-point NRS to obtain self-reported hand pain, hand stiffness and Patient Global Assessment of disease activity and disease activity affecting the activities of daily living. To help capture potential changes at the 3- and 6-month follow-up, 7- and 5-point versions of the Patient Global Assessment of Change Scales are used to self-report disease activity and the management of activities of daily living, respectively.

Maximal grip strength is measured using a Jamar Dynamometer. The participant sits on an armless chair with the shoulder in a neutral position and the elbow 90° flexed. A maximal squeeze of the dynamometer is performed three times for each hand with 15 second breaks, and the average values for each hand will be calculated.

A functional performance test, the Moberg Pick-up Test, is included to help obtain a quantitative assessment of hand dexterity [38]. The test consists of 12 small objects that have to be picked up while time is recorded using a stop watch. The standard protocol by Ng et al. is applied, and the test is performed once with each hand and the eyes open. The 12 objects are in accordance with a description in the paper by Stamm et al. [38].

To measure the thumb web space in a standardised manner, a Grip Size instrument (12 transparent plexiglass cylinders with a diameter from 1 cm to 12 cm) is used. Participants are asked to grip one cylinder at a time, and the largest size where the assessor can see full contact between the cylinder and the total arch of the participant’s thumb and second digit is recorded.

The 15D instrument of health-related quality of life (15D) is a generic, comprehensive, self-administered instrument that captures 15 dimensions (i.e. mobility, usual activities, discomfort and symptoms, distress) with five response categories in each dimension, thereby making it theoretically possible to further describe the 30 billion health states [39]. A set of utility or preference weights will be used to generate the 15D score (single index number) on a 0–1 scale, which will be used as a utility measure in the cost-utility analysis.

### Tertiary outcome measures

At all three time points, the questionnaire includes questions about bilateral vs. unilateral hand pain and which hand is the most painful. At both the 3- and 6-month follow-ups, the individuals report any arm injury, arm surgery or hand joint injections that have occurred over the past three months. An 11-point NRS is used to capture fatigue, while psychological distress at baseline is measured by the General Health Questionnaire (GHQ-20), a widely used screening instrument for measuring non-psychotic psychiatric illness in a general population [40]. Items are scored as the original GHQ score in a bi-modal fashion (0-0-1-1) [49].

A single question is used to measure self-reported work ability: “To what degree is your ability to perform your ordinary work reduced today?”, with the following response alternatives: hardly reduced at all, not much reduced, moderately reduced, much reduced and very much reduced (score range 0–4) [41].

Physical activity is self-reported using the International Physical Activity Questionnaire-Short Form (IPAQ-SF) [42], which is expressed as weekly energy expenditures determined by the expressed metabolic equivalent task minutes per week (METs min/wk) of different categories (sitting, walking, moderate- and vigorous-intensity physical activity and total physical activity score) and physical activity levels (low, moderate and high).

In order to examine exercise self-efficacy, a self-administered questionnaire with 12 statements is used to evaluate how certain the participants are that they are capable of sticking to the exercise programme, even under unfavorable circumstances [43]. The instrument has a 7-point response scale (range 1–7, higher scores reflect higher exercise self-efficacy), but only the first-, middle- and last response options are worded: “Not certain at all”, “Maybe” and “Very certain”, and a mean score is calculated.

The intervention groups are asked to keep an exercise diary that includes a registration of the date and the duration of each exercise session. The individuals report their pain level post-exercise and write comments if any. Maximal grip strength is measured at the group sessions by one repetition for each hand after warm-up, but before performing the exercise programme. Based on the diary notes, the total number of exercise sessions performed will be calculated, and a high compliance will be defined as attendance at more than 75% (three of four) of scheduled group exercise sessions and 60% (22 of 36) of prescribed home exercise sessions in the intervention group, as described in a previous hip OA exercise trial protocol [50].

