**Methods:**

Participants with physician-confirmed hand OA according to the ACR clinical criteria are being recruited from two Norwegian OA cohorts: the population-based “Musculoskeletal pain in Ullensaker Study” (MUST) OA cohort, and the hospital-based Oslo Hand OA cohort. Participants are randomised into an intervention- or control group. The control group receives “usual care”, whereas the intervention group receives a 12-week exercise intervention. The intervention group attends four group sessions and is instructed to perform the exercise program three times a week at home. Adherence will be captured using self-report. During the eight weeks with no group sessions, the intervention group receives a weekly telephone call. The assessments and group sessions are being conducted locally in Ullensaker Municipality and at Diakonhjemmet Hospital, Oslo. Outcomes are collected at baseline, and at 3 and 6 months. The primary outcome measure is self-reported hand activity performance at 3 months post-randomisation, as measured by the Functional Index for Hand Osteoarthritis (FIHOA); and a patient-generated measure of disability, the Patient-Specific Functional Scale (PSFS). Secondary outcome measures are self-reported OA symptoms (e.g. pain, stiffness and fatigue), the Patient Global Assessment of disease activity, measured hand function (e.g. grip strength, thumb web space and hand dexterity) and health-related quality of life. Cost-utility and cost-effectiveness analyses will be conducted.

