8.		**Finger stretch:** Lay the right hand on a flat surface. Use the left hand to apply firm pressure for 30 seconds stretching the 2nd to 5th PIP and DIP joints. Repeat 2 times for each hand.
		If the finger joints are painful: stretch one finger at a time; place the 2nd to 4th finger tips (opposite hand) between the finger joints of the 2nd finger; press for 30 seconds.

*The person on the images has consented for the images to be published.

The intervention group attends one group session per week and does two home sessions per week in weeks 1–3. During weeks 4–7 and 9–12 they do three sessions per week on their own. There is a “booster” group session in week 8 to ensure adherence and to individually adjust the exercises. The group sessions last approximately 45 minutes, and are conducted in the afternoon in the locations of the Ullensaker Primary Health Care and at Diakonhjemmet Hospital. SMS reminders are sent one day in advance, and the intervention group additionally receives a weekly telephone call in the weeks without group sessions (weeks 4–7 and 9–12) for individualised advice that addresses the exercises and encourages programme adherence.

The intervention group keeps the exercise equipment after the intervention period and decides themselves if they want to continue performing the exercise programme. Moreover, no advice is given to the control group at this time, but after the 6-month follow-up, the control group is provided with exercise equipment and instructions in the exercise programme. The Ullensaker cohort will most likely be naïve to hand exercises, while some of the Oslo Hand OA cohort may have received instructions at Diakonhjemmet Hospital Outpatient Clinic in 2007/2008. The Oslo Hand OA cohort control group participants will be asked whether they have received instructions in hand exercises before. At the two follow-ups all participants in the control group will be asked whether they have performed hand exercises in the past 3 months.

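### The high-compliance cut-offs do not match the trial's own session counts: 36 is not the number of home sessions in the Intervention schedule, and three of four is not more than 75%

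*Protocol article*

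**What the plan says.** The last paragraph of Tertiary outcome measures defines high compliance in the intervention group by two conditions, one on group sessions and one on home sessions: "attendance at more than 75% (three of four) of scheduled group exercise sessions and 60% (22 of 36) of prescribed home exercise sessions". The text attributes the rule to the protocol of an earlier hip OA exercise trial.

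The Intervention section gives the only week-by-week schedule. The intervention group "attends one group session per week and does two home sessions per week in weeks 1–3". Then: "During weeks 4–7 and 9–12 they do three sessions per week on their own". For the remaining week it says "There is a “booster” group session in week 8" and gives no number of home sessions.

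The Methods part of the Abstract describes four group sessions and says that participants are "instructed to perform the exercise program three times a week at home", over a 12-week programme.

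**The concern.** A compliance threshold given both as a percentage and as a count should yield the same cut-off either way. Here neither condition does. The home denominator of 36 does not follow from the Intervention schedule, and the group percentage excludes the count placed beside it.

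At stake is the reported proportion of highly compliant participants. The programme is mostly done at home and is compared with usual care, so that proportion is one of the descriptive figures a reader will use to judge whether a weak or null result reflects the programme or its uptake. If the rule is settled only after the diaries have been read, the choice of cut-off could also be influenced by the data.

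**Working it through.** **Inputs.** From Intervention: 2 home sessions per week in weeks 1–3, 3 per week in weeks 4–7 and 9–12 (8 weeks), and 4 group sessions (weeks 1, 2, 3 and 8). From the Abstract: 12 weeks, three times a week at home. From Tertiary outcome measures: 60%, 22 of 36; more than 75%, three of four. Assumption: week 8 has between 0 and 3 home sessions, because no number is stated.

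**The plan's own figure.** 0.60 × 36 = 21.6, rounded up to 22; 22/36 = 61.1%. The 22 therefore follows from the 36. The question is whether 36 is the number of home sessions.

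**Home sessions in the Intervention schedule.** Stated explicitly: 3 × 2 + 8 × 3 = 6 + 24 = 30. Adding week 8:

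| Home sessions in week 8 | Home total | Home + 4 group | 60% of home total | Cut-off (rounded up) | 22 as share of home total |
|---|---|---|---|---|---|
| 0 | 30 | 34 | 18.0 | 18 | 73.3% |
| 1 | 31 | 35 | 18.6 | 19 | 71.0% |
| 2 (as in weeks 1–3) | 32 | 36 | 19.2 | 20 | 68.8% |
| 3 | 33 | 37 | 19.8 | 20 | 66.7% |

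No row gives 36 home sessions. With two home sessions in week 8, 36 appears as the total of home and group sessions (32 + 4 = 12 × 3).

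**Home sessions from the Abstract.** Read literally, 3 × 12 = 36 home sessions, plus 4 group sessions = 40. This agrees with the 36 in the compliance rule but conflicts with the two home sessions per week that the Intervention section gives for weeks 1–3.

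**Who is affected, if only home sessions count toward the 22.** With 32 prescribed, participants with 20 (62.5%) or 21 (65.6%) home sessions meet 60% but fail the 22-session count. With 30 prescribed, the same holds for 18 to 21 sessions (60.0% to 70.0%).

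**If group sessions also count toward the 22.** A participant who attended three group sessions needs 22 − 3 = 19 home sessions, and one who attended all four needs 18. Against 32 prescribed home sessions these are 59.4% and 56.3%, so the rule would be slightly lenient rather than strict. Against 30 they are 63.3% and 60.0%.

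**Group condition.** 3/4 = 75.0%, which is not more than 75%. With four sessions, only 4/4 = 100% exceeds 75%. The words require four sessions and the bracket accepts three.

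**The case against.** The strongest reply is that little depends on this rule. High compliance is a descriptive label on a tertiary measure in one arm. No analysis in the document uses the 75%/60% cut-off: the exploratory sub-group analysis under Data analysis requires attendance at all four group sessions and completion of all home sessions. Concordance is also to be described by exercise frequency and duration. A reader might infer that the cut-off defines the adherent group for an efficacy analysis; the document does not support that. This part of the reply stands and limits the importance of the point.

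Second, a reader might take it as shown that 36 is the home count with the four group sessions added by mistake. That is plausible, because 32 + 4 = 36, but it is an inference. It needs two home sessions in week 8, which are not stated, and the Abstract offers another route to 36. What the text supports is that three sections disagree.

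Third, a reader might say that participants will certainly be misclassified as non-compliant. The direction depends on whether the 22 counts home sessions only. The sentence names home sessions as the denominator, but its opening refers to the total number of sessions performed, so the numerator is not beyond doubt. For the same reason, one cannot claim both that group sessions are counted twice and that people with 20 or 21 home sessions fail.

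Fourth, the bracketed three of four probably shows what was meant, since full attendance is reserved for the exploratory sub-group. That is a fair reading, but the sentence still states two incompatible thresholds. The source in an earlier protocol does not help either: percentages can be borrowed, but counts must fit this trial's schedule.

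**Conclusion.** The point holds as an internal contradiction with limited consequences. The Intervention schedule gives 30 explicit home sessions, and 30 to 33 over the assumed range of 0 to 3 in week 8. The denominator of 36 matches none of these and fits only the Abstract's wording or a total that includes group sessions. If the 22 counts home sessions alone, the home criterion is 67% to 73% of the Intervention schedule instead of 60%. The participants affected are those with 20 or 21 home sessions if 32 or 33 are prescribed, 19 to 21 if 31, and 18 to 21 if 30. The group criterion is contradictory without any assumption, and everyone who attends exactly three sessions is affected.

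Only the descriptive compliance rate in the intervention arm changes. The intention-to-treat analysis and the sample size do not depend on it. The exploratory sub-group does not use this cut-off, but its requirement of all home sessions needs the same agreed count.

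**What to change.** Reconcile the Abstract, Intervention and Tertiary outcome measures on the number of prescribed home sessions, and state the number for week 8. This review takes no position on which schedule is right. Then do one of two things: apply 60% to the agreed home-only count and print the resulting integer, or relabel the criterion as 22 of 36 total sessions if the agreed total is 36. State in either case whether group sessions count toward the numerator. Change the group criterion to at least 75% (three of four), so that the percentage matches the stated count. Use the same home count for the exploratory sub-group.

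The cost is a few words and one derivation rule, ideally fixed before the diaries are analysed. The exercise diaries and group attendance already hold the data needed, so nothing more has to be collected.

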### Adverse effects or events

Adverse events related to exercises for people with hand OA are not consistently studied, but the risk is considered to be low if the suitability of the exercise for the individual is appropriately assessed by a trained health professional [8,51]. Should they occur, adverse events related to the exercise intervention are documented by the type and duration, and information on this is collected and registered during telephone counseling and from the exercise diary.

#### Direct and indirect costs

Based on a validated cost diary and a previous study [52,53], a questionnaire was developed to collect information on resource use. Number of sick leave days and absence from non-paid work is reported over the previous three months. Furthermore, health-care utilisation for the previous three months is self-reported as number of visits to relevant health-care providers. They also report any medication taken for hand OA, as well as medical or technical equipment purchased during the past three months. The intervention group fills in an extra questionnaire targeting costs for attending the group sessions (i.e. travel distance, transportation method, public transportation cost if applicable, work absence or travel escort).

### Statistical analyses

#### Data analysis

Demographic and clinical characteristics as well as other baseline data are being collected and will be presented to assess the baseline comparability of the two groups. These variables will also be compared for those participants who withdraw from the study and those who remain. Parametric and non-parametric statistical analysis models will be used depending on the distribution of the variables.

The intention-to-treat principle (ITT) will be followed in the primary analyses of data, and will include all participants, also those who have missing data and those who are not fully compliant with the protocol. Descriptive statistics will be presented for each group as the mean change (standard deviation, 95% confidence intervals) in the outcomes from baseline to each time point. Differences in mean change from baseline to each time point will be compared between groups, using linear mixed models or generalised linear regression modeling, adjusting for baseline levels of the outcome measure. Model assumptions will be checked by standard diagnostic plots, and improvements in the intervention and control group based on the perceived ratings of change will be compared using logistic regression, and presented as odds ratios with 95% confidence intervals. Additionally, the number of “responders” in the two groups will be compared using the OMERACT-OARSI responder criteria [54]. A participant will be classified as a responder if one of the following is fulfilled:

1) High improvement:

•≥50% improvement + absolute change of ≥2 in self-reported hand pain (NRS, 0–10), OR

•≥50% improvement + absolute change of ≥6 in self-reported hand activity performance (FIHOA, 0–30);

OR

2) Improvement in at least 2 of the 3 following:

•≥20% improvement + absolute change ≥1 in self-reported hand pain

•≥20% improvement + absolute change ≥1 in Patient Global Assessment of disease activity (NRS, 0–10)

•≥20% improvement + absolute change ≥6 in self-reported hand activity performance (FIHOA)

An exploratory sub-group analysis will be completed to examine the effectiveness of the exercise programme for those participants attending all group sessions and performing all home sessions. This analysis will only be completed if there are sufficient participants attending all four treatment sessions and performing all home sessions. Treatment concordance will also be evaluated descriptively by self-reported exercise frequency and duration at the 3- and 6-month follow-up.

Exact analyses utilising the binominal distribution will be used to assess the success of outcome assessor blinding (with 95% confidence intervals); no statistical adjustment will be made for multiple testing, and all tests will be two-sided and carried out at the 5% level of significance. Any changes to the study design or analysis plan will be documented with full justification.

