### Participants

We aim to recruit 150 persons with hand OA from two different OA cohorts:

1) The Musculoskeletal pain in Ullensaker STudy – Osteoarthritis cohort (MUST OA), a cohort of persons with OA in their hands, hips and/or knees derived from a population-based postal survey sent to all inhabitants between 40 to 79 years of age (n = 12,370) in Ullensaker Municipality in 2010-2011[24]. Approximately 60% of the individuals with self-reported hand, hip or knee OA have attended a comprehensive clinical examination at Diakonhjemmet Hospital.

2) The Oslo Hand OA cohort, which is a cohort of Diakonhjemmet Hospital patients between the ages of 60 and 80 years enrolled between 2000 and 2002 [25].

Among these, persons with hand OA in accordance with the inclusion and exclusion criteria (Table 1) are being recruited to this RCT, and the recruitment process is outlined in Figure 1. Participant eligibility is checked by the principal investigator (NØ), using the clinical examination data for the MUST OA cohort, and by telephone screening among the Oslo Hand OA cohort. Eligible persons receive written information and a request to participate in the RCT, and baseline measurements are taking place on a regular schedule, with 12–18 participants each time.

**Table 1 T1:** Criteria of inclusion and exclusion

**Inclusion criteria**	**Exclusion criteria**
• Persons with hand OA according to the ACR classification criteria for clinical OA [26]:	• Persons with a cognitive dysfunction;
◦ Pain, aching or stiffness in the hand and 3 of the following:	• Persons who do not understand the Norwegian language;
◦ Hard tissue enlargement involving at least 2 of 10 selected joints	• Persons with inflammatory rheumatic diseases (e.g. rheumatoid arthritis, ankylosing spondylitis) or cancer;
◦ Hard tissue enlargement of at least 2 DIP joints.	• Persons who have recently experienced severe trauma;
◦ Less than 3 swollen MCP joints	• Persons who have recently undergone OA surgery or other major surgery;
◦ Deformity of at least 1 of the 10 selected joints	• Persons who have received steroid injections in their hand joints during the previous two months.
OR uni-/bilateral OA in the CMC1 joint	
• FIHOA* total score ≥5	
• Access to a telephone	

*The functional index for hand osteoarthritis (FIHOA, range 0–30 (0 = best activity performance, 30 = poor activity performance).

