### Sample size

The primary outcome measure FIHOA sum score (range: 0–30 points) was used to estimate sample size. Using a minimal clinically important change (MIC) of three points (10%) (sd 6.2), with a significance level of 0.05 (2 tailed) and a power of 80%, we estimated that 68 persons will be needed in each group. To allow for a 10% drop-out rate, 75 persons will be included in each group.

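### The second responder criterion keeps the FIHOA threshold at 6 of 30 points while its pain and global items use 10% of the scale, so it undercounts responders in an additional analysis

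*Protocol article*

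**What the plan says.** The Data analysis section adds a comparison of the number of responders to the main comparison of mean change, naming the OMERACT-OARSI criteria and then spelling out the rule.

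- First tier, either of two: "≥50% improvement + absolute change of ≥2 in self-reported hand pain (NRS, 0–10), OR" the function item "≥50% improvement + absolute change of ≥6 in self-reported hand activity performance (FIHOA, 0–30").
- Second tier: the counting rule is "Improvement in at least 2 of the 3 following". For pain, the item is "≥20% improvement + absolute change ≥1 in self-reported hand pain". For the global rating, it is "≥20% improvement + absolute change ≥1 in Patient Global Assessment of disease activity (NRS, 0–10"). For function, it is "≥20% improvement + absolute change ≥6 in self-reported hand activity performance (FIHOA").

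Two other places bear on the function item. The Sample size section uses a "minimal clinically important change (MIC) of three points (10%) (sd 6.2"). Table 1 under Participants admits persons with a FIHOA "total score ≥5".

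No reason is given for holding FIHOA at 6 in the second tier.

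**The concern.** The second tier is meant to capture a smaller improvement spread over more than one domain. Its pain threshold is half the first-tier value and its global threshold is the same share of the scale as pain. Only function, which is the trial's primary construct, keeps the first-tier absolute value. The protocol prints the number, so a programmer will code it as it stands. At stake is how many participants are called responders, and whether a FIHOA gain of the size the plan itself calls minimally important can count towards response.

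**Working it through.** **Inputs.** Thresholds and scales come from Data analysis, the entry minimum of 5 from Table 1, and the minimal important change of 3 and SD of 6.2 from Sample size.

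**The plan's own figures.** 3/30 = 10%, as stated. The sample size reproduces: 2 × (1.960 + 0.842)² × 6.2² / 3² ≈ 67.1, rounded up to 68 per group. The responder rule does not enter that calculation.

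**Step 1: absolute thresholds as a share of range.**

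| Item | First tier | Second tier |
|---|---|---|
| Pain | 2/10 = 20% | 1/10 = 10% |
| Global assessment | not used | 1/10 = 10% |
| FIHOA | 6/30 = 20% | 6/30 = 20% |

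At the scaling of the other second-tier items, FIHOA would be 0.10 × 30 = 3.

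**Step 2: does the relative clause act?** The highest FIHOA baseline is 30, and 6/30 = 20%. At any lower baseline, 6 points is more than 20%, so the 20% clause never excludes anyone. In the other items it does some work: 1 point of pain is below 20% once baseline pain exceeds 5, and 6 FIHOA points is below 50% once baseline FIHOA exceeds 12.

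**Step 3: smallest qualifying whole-point FIHOA gain, by baseline.**

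| Baseline | First tier (≥50% and ≥6) | Second tier as written (≥20% and ≥6) | Second tier with ≥3 |
|---|---|---|---|
| 5 | not attainable | not attainable | 3 |
| 6–12 | 6 | 6 | 3 |
| 13–15 | 7–8 | 6 | 3 |
| 16–20 | 8–10 | 6 | 4 |
| 21–25 | 11–13 | 6 | 5 |
| 26–30 | 13–15 | 6 | 6 |

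At baselines 6 to 12, 6 points is already at least 50% (6/12 = 50%). Anyone meeting the second-tier item is therefore a first-tier responder, and the item adds nobody. From 13 upward it is looser than the first tier. From 26 upward the choice between 3 and 6 makes no difference.

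**Step 4: who changes class.** A participant must meet all three conditions:
- a FIHOA gain of 3 to 5 points that is at least 20% of baseline;
- exactly one of the second-tier pain and global items;
- no first-tier pain response.

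A hypothetical case: FIHOA from 12 to 8 (4 points, 33%), pain from 5 to 4 (1 point, 20%), global unchanged. As written this is a non-responder; with ≥3 it is a responder.

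**Step 5: illustrative size for the FIHOA item alone.** Assume normally distributed change with mean gain 3 in one arm and 0 in the other, ignoring the relative clause and the floor of the scale. The SD of change is assumed; the protocol does not say that 6.2 is an SD of change.

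| SD of change | Meets ≥6 (gain 3 / gain 0) | Meets ≥3 (gain 3 / gain 0) | Gap (gain 3 / gain 0) |
|---|---|---|---|
| 4 | 22.7% / 6.7% | 50.0% / 22.7% | 27.3 / 16.0 points |
| 5 | 27.4% / 11.5% | 50.0% / 27.4% | 22.6 / 15.9 points |
| 6.2 | 31.4% / 16.7% | 50.0% / 31.4% | 18.6 / 14.7 points |

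The gaps are ceilings on the shift in responder rates under this model, because only the subset in Step 4 changes class.

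**The case against.** Several stronger readings are tempting, and the documents do not carry them.

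- A reader might infer that second-tier function is as strict as the first tier throughout. It is not: at baseline 20 the first tier needs 10 points and the second 6. The two coincide only at baselines 6 to 12, and neither can be met at 5.
- The baseline-5 problem is not peculiar to the second tier, since the first-tier FIHOA item cannot be met there either. Such a participant can still respond through first-tier pain, or through pain and global together.
- A reader might infer that the between-group comparison is biased. The same rule applies to both arms. On the Step 5 figures the item's odds ratio is slightly higher at ≥6 than at ≥3: at SD 5, (0.274/0.726)/(0.115/0.885) = 2.90 against 1/(0.274/0.726) = 2.65. The same arithmetic gives 4.09 against 3.41 at SD 4, and 2.28 against 2.18 at SD 6.2. Counts and the risk difference fall (at SD 5, 22.6 to 15.9 points), which is a loss of sensitivity.
- A reader might infer that the rule departs from the published criteria it names. That source is not at hand, so this cannot be said either way.
- The minimal important change of 3 is used to size a between-group difference; the protocol does not say that it sets an individual cut-off. A redundant 20% clause is suggestive, and by itself changes no classification.

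All of this stands. It limits the consequence and the severity. It does not explain why one of three parallel items is scaled at twice the share of range of the other two.

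**Conclusion.** The point holds as an internal inconsistency in a printed rule. The second-tier FIHOA threshold is 20% of range where its companion items are 10%, and it is twice the plan's minimal important change. It leaves a relative clause without effect and adds no responders at baselines 5 to 12. Relative to a rule scaled consistently, responder counts are too low in both arms, and some real improvement goes unrecorded.

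The documents do not fix the size. It depends on the baseline FIHOA distribution, the SD of change, and how FIHOA, pain and global changes go together. The item-level gaps of roughly 15 to 27 points are upper limits under the stated normal model and should not be read as errors in the responder rate.

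The responder comparison is additional and is not listed among the outcomes in Tables 3 and 4. The primary comparison of FIHOA and PSFS and the sample size are untouched. Severity is minor to moderate.

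**What to change.** Before unblinding, check the second-tier FIHOA value against the cited responder criteria. Then change it from ≥6 to ≥3 (10% of 0–30) in the second tier only, leaving ≥6 in the first. Record the change with its reason, as the end of the Statistical analyses section already requires for any change to the analysis plan. If 6 is intended, state why and report the ≥3 version as a sensitivity analysis.

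The cost is one number in the plan and in the responder program. No extra data or participants are needed, because status can be recomputed from scores already collected. Settling it before allocation is revealed matters because a threshold chosen later could be seen as chosen on the results.
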